## Abstract

**Background:**

Schools are a central place in the lives of both children and teachers, with the potential to counteract current challenges such as a physical and emotional disconnection from nature, insufficient physical activity, and increased social isolation. Concepts like Education Outside the Classroom (EOtC) offer a variety of approaches and are already established in the curriculum in other countries, while in Germany EOtC is still in the early stages of implementation. Previous studies have focused on the effects of EOtC on students, with little attention paid to teachers, environmental perception, or behavioural analyses. This study aims to evaluate the impact of EOtC on teachers’ stress level, teachers’ well-being and physical activity, pupils’ cognitive performance, school-related well-being, basic psychological needs and classroom behaviour. In addition, this study investigates how the biodiversity of selected outside learning environments affects pupils’ and teachers’ nature connectedness, appreciation of nature and species knowledge.

**Methods:**

This study protocol describes an exploratory, quasi-experimental, interdisciplinary study conducted in a total of 33 schools throughout Germany. Data collection will be carried out from September 2025 to November 2026. The first results of the data collection are expected in October 2026. It includes approximately 50 EOtC teachers, 50 non-EOtC teachers, 50 EOtC classes, and 18 non-EOtC classes with for intra- and interindividual comparisons. Data collection covers aspects from the fields of health, ecology, school pedagogy, and sociology and includes both pupils and teachers as target groups, as well as the various outdoor learning environments. For pupils and teachers, the study examines the effects of EOtC on nature connectedness, appreciation of nature, and plant and animal species knowledge. This is assessed twice per school year with questionnaires and compared to control classes within the same schools. In addition, for pupils, cognitive performance, measured by electroencephalography (EEG), school-related well-being, and basic psychological needs – both assessed via questionnaires – will be analysed. For teachers, stress levels, emotional well-being, and physical activity will be assessed using salivary cortisol samples, accelerometery, and questionnaires on both EOtC and regular teaching days, enabling intraindividual analyses. Moreover, teaching characteristics will be documented, and video-based analyses of social interactions between teachers, pupils, the outdoor learning environment, and teaching objects are conducted. Finally, biodiversity at the outdoor learning sites and their effects on the other study variables (e.g., nature connectedness, appreciation of nature, species knowledge and well-being of pupils and teachers) will be statistically analysed.

**Discussion:**

This interdisciplinary study design provides a realistic analysis of the potential effects of EOtC on pupils, as well as teachers, while minimizing interference with the regular teaching process. A strength of this study is the consisted inclusion of teachers as a target group, as well as the ecological perspective and the use of innovative survey methods such as the recording of biodiversity, the video analysis of interactions and the analysis of lesson characteristics in the context of EOtC. This study will thus contribute to closing central research gaps in the German context and provide valuable insights for international EOtC research.

## 1. Introduction

Children and adolescents in Germany, as in other Western countries, face a variety of social and health-related challenges, such as insufficient physical activity (PA) [1], declining mental health [2] and increasing social isolation [3]. Additionally, an increasing alienation from natural spaces has been observed [4,5], which is causing a decrease in the potential positive effects of nature experiences and opportunities for social interaction and PA. Schools represent a central living environment for children and adolescents: pupils spend an average of 20–30 hours per week in class [6], plus additional time spent on homework or extracurricular activities. Thus, schools could be an effective starting point to counteract the loss of nature experiences – often referred to as the ‘extinction of experience’ – as well as related health and social challenges. At the same time, the teachers also often work well beyond the mentioned hours of classroom teaching [7,8]. Teachers are increasingly exposed to high workloads, time pressure, and long periods of sedentary behaviour (SB), while at the same time having to deal with the social and emotional dynamics of their pupils, as well as their own [8,9]. In response to these growing demands for both pupils and teachers, there is increasing interest in educational approaches that address and improve the deficits regarding nature connectedness, PA, social interaction and psychosocial well-being in both pupils and teachers. Although there are many different concepts, add-on programs often fail due to limited sustainability. Instead, concepts that can be seamlessly integrated into everyday school life, are preferred. One of these concepts with diverse social, pedagogical, health, and nature-related potential is *Education Outside the Classroom* (EOtC). This concept provides a shift in the learning environment, which can provide valuable new impulses for both pupils and teachers. Such temporary spatial changes have been shown to foster well-being, support social interaction and, depending on the setting, strengthen awareness and appreciation for the environment [10,11].

A wide range of concepts and practices, such as *outdoor education, forest school, friluftsliv* and *learning outside the classroom* have emerged internationally and tap into the potential offered by temporary changes of location. Although these concepts share the idea of relocating educational activities outside school buildings, they differ in many ways, including pedagogical emphasis, cultural background and contextual adaptation [12,13], as well as their structure, goals and implementation style. Within this diverse field*,* EOtC has developed into a curriculum-aligned teaching context that takes place outside the traditional classroom in natural, cultural, historical, or urban environments and is embedded in the regular school schedule [11,14]. In this context, EOtC should not be confused with occasional school trips or project days, but rather understood as a structured, ongoing part of weekly or biweekly lessons lasting at least four hours, which are usually conducted over several consecutive months or longer, with the regularity of this format expected to reinforce potential effects. While EOtC is already an integral part of the teaching culture in some countries, such as Denmark, Norway, Sweden and New Zealand, there are only a few schools in Germany so far that implement the concept. Because of its characteristics of regularity and long-term nature, EOtC has the potential to cause sustainable changes. Previous research showed that EOtC can have positive effects on pupils’ social well-being [11,15], stress regulation [16,17], intrinsic learning motivation [18,19], understanding of nature and environmental attitudes [20,21], PA [22,23] and academic performance, such as reading or writing skills [24]. These results suggest that EOtC may have the potential to combine health promotion, learning support, social interactions, and positive experiences in nature.

Even though existing research already highlights important effects of EOtC on pupils, further questions remain unanswered. For example, how different EOtC environments may influence pupils’ knowledge, basic psychological needs, nature connectedness and social interactions, as well as those with nature. It is important to understand how pupils interact not only with the environment but also with their classmates, as these interactions influence not only individual outcomes but also the overall learning environment. Furthermore, most research to date has focused primarily on the impact of EOtC on pupils, while teachers and the demands of their work environment have received comparatively little attention.

Therefore, this EOtC study is an interdisciplinary research project, aiming to investigate the potential effects of regular EOtC on health-related, social, pedagogical, and ecological outcomes in German schools and to examine how these outcomes are interrelated across these domains where possible. Given this thematic range and methodological approach, the study addresses a set of research questions structured across four key domains, which are outlined below.

Health-related research questions:

1. Can intra-individual differences in diurnal cortisol dynamics, specifically the subsequent decline throughout the school day, be observed in teachers on EOtC days compared to regular indoor teaching days?2. What differences in teachers’ hedonic well-being, particularly in terms of positive and negative affects, can be observed on EOtC days compared to regular indoor teaching days?3. What differences in teachers’ physical activity and sedentary behaviour can be observed on EOtC days compared to regular indoor teaching days?4. To what extent is higher work-related quality of life (WRQoL) observed among teachers participating in EOtC compared to those teaching exclusively in indoor settings?5. How do children’s EEG patterns related to attention, stress, and emotional regulation differ between EOtC and regular indoor teaching days?6. Is there another dimension in the construct of BPNs that addresses the fulfillment of the need relatedness through a non-social factor, namely nature relatedness?7. Which effects do BPNs and/or nature relatedness, if considered a separate construct, have on children’s school-related well-being?

Pedagogical research questions:

1. Is there a difference in the extent of the applied teaching principles between teaching in EOtC and classroom teaching?2. To what extent are the different teaching principles applied during teaching in EOtC?3. What kind of changes in teaching, learning and “doing school” occur when teachers and students leave the familiar classroom environment to conduct lessons outdoors in nature?4. How do teachers respond in their instructional and pedagogical practice to the challenges of conducting school lessons outside the classroom?5. Are there differences in student behavior between teaching in EOtC and classroom teaching, specifically in the way they participate in lessons or disengage from educational interactions? What role does nature play in this context?6. How do children with learning disabilities and behavioral emotional disorders respond to EOtC?7. Does EOtC offer the potential to rediscover school as an appealing learning space, which ultimately may restore and promote commitment to school-based learning?

Ecological research questions:

1. Does EOtc lead to higher species knowledge in pupils and teachers?2. Does EOtC lead to higher connectedness to nature in pupils and teachers?3. Does EOtC lead to higher appreciation of nature in pupils and teachers?4. Does higher biodiversity of outdoor learning sites lead to higher species knowledge, connectedness to nature and appreciation of nature in pupils and teachers?5. Does higher structural complexity (e.g., higher forest development stages and higher deadwood amount) of outdoor learning sites lead to higher species knowledge, connectedness to nature and appreciation of nature in pupils and teachers?

With this interdisciplinary and multi-methods approach, the project represents a novelty in EOtC research in Germany and enriches international research on EOtC by addressing vital questions. Given the complexity of EOtC as an educational and environmental intervention, an interdisciplinary approach like this is essential and calls for a transparent description of the methodological approach. This study protocol describes the design, methods, and analysis strategies for this comprehensive, interdisciplinary project.

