### 2.3. Recruitment process and participants

As mentioned above, EOtC is defined as regular, curriculum-based teaching, which is conducted in a natural, cultural, historical or urban environment [11,14]. This definition builds the base for inclusion and exclusion criteria when identifying schools, classes and teachers to participate in this study. Schools were included in the study if EOtC was carried out for at least four hours every two weeks. This threshold was chosen to ensure that participating classes engage in EOtC for approximately one full day per week in the case of elementary school and at least half a school day in the case of secondary schools. No additional exclusion criteria were defined. The frequency is intended to emphasize that EOtC is not a sporadic activity, but rather a consistent and integral element of the pupils’ and teachers’ routine. Schools in all of Germany’s federal states were contacted in order to represent as many federal states, school types and associated learning locations as possible. A total of three different sources of contact were used to recruit schools for data collection: Some contacts already existed to individual schools implementing EOtC in Germany through previous projects and conference attendance by individual scientists. Similar collaborations with schools already existed with the external project partner, Schutzgemeinschaft Deutscher Wald (SDW). In addition, an internet search was carried out for schools which have implemented the concept of EOtC. In the recruitment phase from beginning of January to the end of July 2025, 101 schools were initially contacted. Of these, 45 schools showed interest. 13 schools actively declined, citing reasons such as lack of time, insufficient capacity or no specific reason. Four schools did not meet the inclusion criteria. 43 schools did not respond at all. Five schools withdrew after initially agreeing to participate, resulting in a final sample of 36 schools. A flowchart mapping the various stages of recruitment, number of excluded and included schools, as well as reasons for inclusion/exclusion and the numbers of participating pupils and teachers is shown in Fig 1. To obtain a precise overview of the classes, pupils and teachers involved, network meetings were held at which the planned surveys were first presented, and the interest of the individual teachers was then queried. Emails were sent to the schools that were unable to attend the meetings to obtain a final sample size. In addition to EOtC classes and teachers, corresponding control classes and teachers were also sought at each participating school to include them in the data collection as both intra- and inter-individual comparisons are planned in the study design.

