#### 2.5.2. Teachers’ physiological stress.

Physiological stress will be measured by salivary cortisol, a validated biomarker of the hypothalamic–pituitary–adrenal axis (HPA) activity that has previously been applied in educational settings [17,33,34]. Saliva samples will be collected by the teachers themselves using Salivettes^®^ (Sarstedt, Germany), with individual sampling kits provided to all participants to ensure standardized collection. To account for intra-individual variability in cortisol secretion, a repeated-measures design will be used. The sampling will be conducted on four separate days, comprising two days of EOtC sessions and two days of classroom teaching. On each day, the cortisol awakening response (CAR) will be measured as an individual baseline reference. This includes one saliva sample immediately upon awakening and a second sample 30 minutes later for men and 45 minutes later for women to capture the peak cortisol level. The adjusted timing accounts for gender-specific differences in the temporal dynamics of the cortisol response to awakening [35,36].

In addition, three daytime samples will be collected on each measurement day at standardized time points (8:00 AM, 10:15 AM, and 12:30 PM) to determine the diurnal cortisol pattern and allow comparisons across days and conditions. After collection, samples will be stored during the day in the provided insulated bag and frozen in a household freezer in the evening prior to collection by study staff. To account for potential confounding effects of sleep duration and sleep quality on cortisol secretion, sleep-related variables will be assessed separately.

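### The four-hour minimum is set per lesson in one section and per fortnight in another, and EOtC measurement days are not linked to session length or clock time, so the whole-day label may dilute the teacher cortisol contrast

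*Protocol article*

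**What the plan says.** Three parts of the protocol article bear on this point.

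- **Definition.** Section 1 presents EOtC as "a structured, ongoing part of weekly or biweekly lessons lasting at least four hours". Here the four hours belong to the lesson.
- **Entry rule.** Section 2.3 states: "Schools were included in the study if EOtC was carried out for at least four hours every two weeks". Here the four hours belong to a two-week period. The section restates the definition without any lesson length and says of it: "This definition builds the base for inclusion and exclusion criteria when identifying schools, classes and teachers to participate in this study". It then adds: "No additional exclusion criteria were defined". The stated purpose of the threshold is "to ensure that participating classes engage in EOtC for approximately one full day per week in the case of elementary school". For secondary schools the aim is put lower, at half a day or more.
- **Teacher measurements.** Section 2.5.2 plans sampling on four days, "comprising two days of EOtC sessions and two days of classroom teaching". Besides two samples around awakening, "three daytime samples will be collected on each measurement day at standardized time points (8:00 AM, 10:15 AM, and 12:30 PM"). Table 1 lists the affect questionnaire (PANAS) at the same frequency as cortisol, five times a day on two EOtC and two regular days. Section 2.5.5 has accelerometers worn on four days, two of them with EOtC.

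Section 2.8.1 plans linear mixed models for cortisol and names sleep quality and chronotype as examples of covariates.

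**The concern.** Health questions 1 to 3 compare teachers' EOtC days with their indoor days. The exposure in that comparison is a label on the whole day, while the saliva samples sit at fixed clock times. The label describes a given sample well only if the session is long enough, and placed so, that the sample falls within it or after it.

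The entry rule does not secure this. Two 2-hour or four 1-hour sessions per fortnight also reach four hours. A session of any length may sit early, late or in the afternoon. Samples taken before the session starts cannot reflect the session itself, yet they would be analysed as EOtC samples. If that happens in part of the sample, the estimated difference in cortisol decline is pulled toward zero. A null result could then mean no effect, or sampling at the wrong time relative to exposure, and the data would not tell the two apart.

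**Working it through.** **Inputs**

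- Sample times 8:00, 10:15 and 12:30 (section 2.5.2). The gaps are 2.25 h each and the span is 4.5 h.
- Four hours per lesson (section 1), or four hours per two weeks (section 2.3).
- Class time of 20 to 30 hours per week (section 1). With a five-day week, which is my assumption, a school day is 20/5 = 4 h to 30/5 = 6 h and half a day is 2 to 3 h.

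**Step 1: does section 2.3 settle the unit?**

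The threshold averages 4 h / 2 weeks = 2 h per week. Against one school day per week that is 2/6 = 33% to 2/4 = 50%. The rule alone does not reproduce the full day per week given as its purpose for elementary schools, which would need 2 × 4 = 8 to 2 × 6 = 12 h per fortnight. The half day given for secondary schools (2 to 3 h) is shorter than the four-hour lesson of section 1. The stated purpose therefore does not show that four hours per session was meant.

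**Step 2: how many daytime samples can fall inside one session?**

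A session of length L starting at time a contains a sample at time s if a ≤ s ≤ a + L.

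- L ≤ 2 h: L is below the 2.25 h gap, so at most one sample falls inside. There may be none; a session from 8:05 to 10:05 is an example.
- L = 4 h: L is at least 2.25 h but below 4.5 h, so at most two fall inside. All three need a session spanning 8:00 to 12:30.
- Start after 12:30, any length: none falls inside, and all three precede the session.

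**Step 3: how does this vary with start time?**

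Start times were taken minute by minute from 8:00, with the session ending by 13:00 or by 16:00. The 8:00 start and both end times are assumptions.

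| Session length | Start times with no sample inside, end by 13:00 | End by 16:00 |
|---|---|---|
| 1 h | 61% | 71% |
| 1.5 h | 42% | 53% |
| 2 h | 15% | 33% |
| 4 h | 0% (one or two inside) | 0% (one or two inside) |

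Check of the 2 h row, end by 13:00: there are 181 possible start minutes (8:00 to 11:00). Starts from 8:01 to 8:14 and from 10:16 to 10:29 miss every sample, which is 28 minutes, and 28/181 = 15%. For an end by 16:00 there are 361 start minutes (8:00 to 14:00). The starts from 12:31 to 14:00 add 90, and (28 + 90)/361 = 33%.

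These percentages describe possible start times. They do not estimate how many teachers are affected.

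**Step 4: inside is not the same as informative.**

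A sample taken after a morning session can still reflect it. For sessions of up to four hours that end by 13:00, at least one daytime sample always comes after the start. Only a start after 12:30 leaves every daytime sample before exposure.

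**The case against.** The strongest reply is that the two sections are compatible. One four-hour lesson per fortnight satisfies both, section 2.3 calls the definition the base for its criteria, and it explains the threshold in terms of full and half days. This stands in part: a reader might infer a flat contradiction, or that the rule was meant to add up short sessions, and the text supports neither. What remains is that the wording of section 2.3 allows shorter sessions and nothing else in the section excludes them.

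The second reply is that the harm is hypothetical. This also stands. A reader might infer that short or afternoon sessions are present and that days of mostly classroom teaching will be labelled EOtC. The article reports no session lengths or times, so that cannot be shown.

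Third, the questions are posed at day level under real-world conditions. A day with a short session is then a weaker exposure, not necessarily a wrong label. Samples before a session can also anchor the decline, and those after it can carry its effect. This is correct, and it means that the share of the window covered is not a measure of bias. Nor does the sampling-window argument extend to physical activity: accelerometers record continuously, so a session outside 8:00 to 12:30 is still captured.

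Fourth, a journal article may leave session logs to a fuller document. That is fair for the log itself. But this article fixes both the entry rule and the sample times. For the pupil EEG recordings (section 2.5.8) it also asks for the same subject, teacher and time frame in both settings, and it states nothing comparable for teacher cortisol.

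Finally, one might require a session of at least four hours overlapping the sampling window before a day counts as EOtC. That would not solve the problem. A session from 12:00 to 16:00 would pass while covering 0.5/4.5 = 11% of the window, and teachers with shorter sessions would be lost from a group of about 50.

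**Conclusion.** The point holds in a limited form. The four-hour minimum is attached to different units in sections 1 and 2.3. The article does not connect an EOtC measurement day to the length or clock time of its session. With samples at 8:00, 10:15 and 12:30, a session of two hours or less contains at most one of the three and may contain none. A four-hour session contains at most two. A session starting after 12:30 follows all three. Length alone is therefore not the issue; timing matters even when the four-hour lesson is honoured.

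The consequence is possible dilution of the cortisol contrast. The same would apply to momentary affect if PANAS is completed at the saliva times, which is an assumption: Table 1 gives the same frequency but no clock times. The size of the dilution cannot be computed, because session lengths and times are not given. If nearly all sessions start by about 8:00 and last the morning, it is negligible. It grows with the share of late or short sessions.

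**What to change.** 1. Reconcile sections 1 and 2.3: state whether the four hours apply to each session or to the total over two weeks, and make the stated purpose of the threshold agree with that choice.
2. Have teachers record the start and end of EOtC on each EOtC measurement day.
3. Code each cortisol and PANAS record as before, during or after the session, and accelerometer time as inside or outside it.
4. Keep the day-level EOtC versus classroom contrast with all teachers; exclude no one for a short session. Add the session-timed exposure to the mixed model, or specify it as a sensitivity analysis. Keep sampling time in that model, so that each record is compared with the same clock time on classroom days and the before/after coding is not confused with the normal decline over the day.
5. Report the distribution of session lengths and start times, so that a reader can judge how well the day label fits.

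The cost is two clock times per EOtC measurement day. With two such days that is four per teacher, or about 200 for some 50 EOtC teachers, plus slightly more analysis work. If sessions turn out to start by 8:00 throughout, every daytime record is during or after the session and little has been spent.
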